Other inpatient services provided by the SIRI Team that fall outside the standard of care for most typical hospital-based ID consult services include the following: 1) Close coordination and frequent communication with hospital case manager/social worker to help guide discharge planning; 2) working to identify funding sources for post-hospital medications and follow-up services; 3) facilitating access to a box of intranasal naloxone immediately before or after discharge; 4) prescribing necessary post-discharge medications, pick-up from pharmacy, and delivery to participants.

If a participant is readmitted to the same hospital during the 4-month intervention period, the intervention team will re-engage with them in the hospital and again provide SIRI team care. If a participant is admitted to a different hospital during the intervention period, the SIRI team will attempt to coordinate with physicians in the non-index hospital to help coordinate post-hospital care. Similarly, while SIRI team provider will not be able to directly provide care to participants while incarcerated, they may attempt to advocate for individuals and communicate with providers in the department of corrections.

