#### Patient navigator component

The patient navigator approach includes five functions: 1) establishing an effective working relationship with the participant; 2) encouraging identification and use of strengths, abilities, and assets; 3) supporting participant control over goal setting and the search for needed resources; 4) viewing the community as a resource and identifying informal sources of support; and 5) conducting case management as an active community-based activity.

The patient navigator goals are to assess and assist participants in four primary domains: 1) Medical: Patient navigators facilitate participants completing antibiotic therapy for their acute infection and help participants meet other medical needs, such as getting to medical appointments, managing medications, and encouraging adherence to treatments. 2)

Substance use: Patient navigators use motivational interviewing techniques to ascertain barriers and facilitators to reducing substance use. They ensure medical treatment for SUD by the medical providers, according to participant desires. They assist with linking to other community substance use and/or harm reduction programs (residential treatment, intensive outpatient, SSPs, etc.). Patient navigators will also conduct outreach to locate missing participants—including homeless encampments and shelters—to continue to provide services. For participants who continue drug use, the patient navigator promotes harm reduction and helps facilitate safer drug use. 3) Housing: For participants experiencing homelessness, patient navigators actively connect participants with local shelters and housing programs and food resources. 4) Access to medical care: patient navigators help participants obtain access to health insurance and other funding sources for ongoing care, especially in the post-intervention period.

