### Intervention discontinuation and cross-over

The intervention continues until 122 days post-randomization. Because the intervention includes active monitoring of participant medical records and ongoing outreach, the intervention will be terminated early only if a participant withdraws consent from the study or dies prior to day 122. Control group participants are not treated by the SIRI team intervention, as outlined in the intervention manual; however, they are permitted to be treated by clinician members of the SIRI team in non-SIRI team contexts. For example, a SIRI team physician is permitted to be the outpatient HIV provider for a control group participant, as long as the care provided falls within the usual treatments provided by that physician and clinic, outside of the context.

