### Outcomes

The primary outcome is a binary measure: a participant is alive with no hospital readmissions 4 months (122 days) post-randomization OR a participant has died or been readmitted to the hospital within 4 months post-randomization. The primary outcome measure is the proportion of those who are alive with no hospital readmission at 4 months post-randomization in the SIRI team intervention compared with TAU. Hospital readmission is defined as either observation or inpatient status in an acute care hospital after discharge from the index hospitalization (i.e., the hospitalization during which randomization occurred). Elective hospital admissions, for example, for planned chemotherapy or elective surgeries, are excluded. Hospital admissions for delivery of a child in pregnant participants will be included as elective admissions. Admission to behavioral health hospitals, medically supervised withdrawal units, or psychiatric-only admissions are also excluded. The primary outcome was chosen to be relevant to patients and healthcare systems. Healthcare utilization outcomes, such as readmission and emergency department visits, will be measured using both EHR data and self-report, confirmed by EHR. At baseline assessment and each follow-up study visit, participants will be asked about healthcare service utilization and if they report receipt of services, a release of information for each relevant institution will be obtained and records requested to confirm self-report. All participants will have the EHR of the study site (*index hospital*) healthcare system queried for health services use. Additionally, any integrated health information exchange services, such as Care Everywhere for Epic, will be queried. Deaths will be determined from EHR data, local medical examiner databases, and information from emergency/secondary contact persons for participants who cannot be located. The secondary outcome related to the primary outcome of the study includes being alive and free from readmission across all study time points (4, 8 and 12 months). Other secondary outcomes are listed in Table 2.

**Table 2 Tab2:** Key secondary outcomes

Outcome	Measure	Time point
Completion of planned antibiotic course	Combination of medical record abstraction and self-report	Assessed at 4-month visit
New or recurrent SIRIs	Combination of medical record abstraction and self-report	4, 8, and 12 months

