For the primary outcome, data lost to missed visits will be supplemented via external records. Confirmation of death from any cause or of participant hospital readmission from the EHR abstraction will be considered a failure. If a participant is lost to follow-up and no records (EHR, medical examiner, emergency contacts’ report) are found to show death or readmission for the duration of the study, the outcome will be considered a success. Missing data is only anticipated for 1) participants who withdraw from the study up to and including study day 122 and who have not signed the consent addendum expressly permitting abstraction to continue, or 2) participants who withdraw from the study at any time during the follow-up period AND who have not signed the consent addendum AND EHR abstraction has not been performed up to and including study day 122 prior to the participant’s withdrawal. At baseline, participants will sign releases for all local health systems that they typically visit. These records will be supplemented by a query of EHR integration services, such as CareEverywhere in Epic Systems. For participants who miss their 4 month visit but attend the 8 or 12 month visit, they will be asked about readmissions dating back to the time of randomization.

A secondary analysis of the hospital readmissions across all time points will be conducted. For this analysis, a Generalized Estimating Equations (GEE) model will be employed with a binomial distribution and logit link as implemented in SAS for the secondary outcomes of proportion of participants alive with no hospital readmissions utilizing all time points. A GEE model is used to control for correlation associated with repeated measures within an individual since the analysis will be a longitudinal one at 4-, 8-, and 12-months. The model will include fixed effects for treatment group, time, the treatment-by-time interaction, site, type of primary drug use (opioid versus non-opioid), and admission to ICU as part of the index hospitalization (ICU versus non-ICU)). The secondary outcome hypotheses are that the proportion of participants alive with no hospital readmissions will be higher in the SIRI Team intervention group vs. TAU group at eight months (and, separately, at twelve months) post-randomization). These two hypotheses will be evaluated each using a two-sided test with an a priori alpha (i.e., type I error) of 0.05.

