Despite the promising pilot study results, success in the HI-SIRI study faces several challenges and potential limitations. The non-blinded nature of the trial may introduce bias, and the reliance on self-reported data for some outcomes could affect the accuracy of the findings; however, self-reported healthcare utilization will be validated against medical record abstraction. The intervention involves substantial contact with the medical team, which could be costly, especially physician involvement. While we do not expect any cross-over of TAU participants into the intervention arm, the development of local SIRI teams, clinician peer education, and leadership could bleed over into the TAU arm with potential to dilute the effect of the intervention. For example, a SIRI team might create an infectious disease screening order set that could start to be used by physicians caring for TAU participants, thereby improving infection screening in both treatment arms. The impact of having a SIRI team in the hospital will be further characterized in the implementation science component of the trial. Finally, loss to follow up is common in trials involving individuals with SUD and we expect even higher among PWID hospitalized with infections. In order to mitigate this risk, participants will only be enrolled if they provide at least minimum pre-defined locator information and participants with no phones will be provided with study phones. Furthermore, the primary outcome is available independent of whether a participant is lost to follow up.

If successful, the HI-SIRI study has the potential to significantly impact the care of PWID with SIRIs by providing a holistic, patient-centered approach that integrates infectious disease and SUD treatment with harm reduction strategies. The findings from this study will have the potential to transform our approach to care for PWID with infections, advancing health for a community long left behind in healthcare innovations.

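### Lost participants with no record are scored as successes, while the intervention adds its own surveillance in one arm: failures may be found more completely under SIRI, which would bias the primary comparison against it

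*Protocol article*

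**What the plan says.** **Scoring rule** (Statistical analysis, Analyses of primary and secondary outcomes). A confirmed death or readmission is a failure. "If a participant is lost to follow-up and no records" in the EHR, with the medical examiner or from emergency contacts "are found to show death or readmission for the duration of the study, the outcome will be considered a success". Missing data are anticipated only for some withdrawals, for example "participants who withdraw from the study up to and including study day 122 and who have not signed the consent addendum". The Discussion expects heavy loss to follow-up, yet says that "the primary outcome is available independent of whether a participant is lost to follow up".

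**Search common to both arms.**
- The index health system's EHR and any health information exchange are queried for everyone (Outcomes).
- Releases are signed at baseline for the local systems a participant usually visits, and those who miss month 4 are asked at month 8 or 12 about readmissions back to randomization (Analyses of primary and secondary outcomes).
- A research outreach worker does street outreach and checks medical records, jail and prison logs and the coroner (Retention).
- Abstraction runs to about 14 months (Measures and timing of follow-up assessments).
- For other institutions, "if they report receipt of services, a release of information for each relevant institution will be obtained" (Outcomes).

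**Added in the SIRI arm only, to day 122.**
- Contact about daily in hospital and about weekly afterwards (Study design and objectives).
- "Because the intervention includes active monitoring of participant medical records and ongoing outreach", the intervention ends early only on withdrawal of consent or death (Intervention discontinuation and cross-over).
- "Patient navigators will also conduct outreach to locate missing participants" (Patient navigator component).
- On admission elsewhere, "the SIRI team will attempt to coordinate with physicians in the non-index hospital" (SIRI team inpatient care).

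Follow-up assessors are not blinded (Allocation concealment and blinding). Event forms are triggered by the site becoming aware of an event (Table 1).

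**The concern.** Under this rule a failure that nobody finds becomes a success. If the share of failures found were the same in both arms, the risk difference would shrink but the test would keep its size. If the share differs by arm, the difference shifts even when the intervention does nothing.

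The treatment itself contains surveillance, and its window is the endpoint window. The failures most exposed are those the common search reaches least well: a readmission at a hospital that is not on the exchange and not covered by a baseline release, or a death outside the local area. For a participant who stops attending, the route through self-report and a new release closes. In the SIRI arm, the team's own contact may still bring such an event to the site's notice. In the TAU arm it is more likely to stay unknown and be scored a success.

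At stake is a real benefit made to look smaller, or missed, and under no effect a raised chance of apparent harm.

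**Working it through.** **Inputs.** From the article: N = 480, two-sided alpha 0.05, and the Table 3 row with success 0.550 (TAU) and 0.674 (SIRI), difference 0.124. Assumed: 240 per arm, since no allocation ratio is stated, and all detection rates.

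**Step 1: reproduce the plan's power.** Power = Φ[(d − 1.96 × SE0) / SE1], with pooled SE0 and unpooled SE1.
- Mean success = (0.550 + 0.674)/2 = 0.612.
- SE0 = √(2 × 0.612 × 0.388 / 240) = 0.0445.
- SE1 = √(0.550 × 0.450/240 + 0.674 × 0.326/240) = 0.0441.
- Power = Φ[(0.124 − 0.0872)/0.0441] = 0.80.

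The same formula gives 0.798 to 0.803 for all eight rows, so Table 3 is reproduced. It treats every failure as found.

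**Step 2: add incomplete detection.** If a share s of an arm's true failures is found, observed success = 1 − (1 − p) × s. With s = 0.90 (TAU) and 0.95 (SIRI):
- TAU: 1 − 0.450 × 0.90 = 0.595.
- SIRI: 1 − 0.326 × 0.95 = 0.690.
- Difference 0.095; SE0 = 0.0437, SE1 = 0.0435; power = 0.59.

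| Share found, TAU / SIRI | Observed difference (points) | Power |
|---|---|---|
| 100% / 100% | 12.4 | 80% |
| 90% / 90% | 11.2 | 73% |
| 93% / 95% | 10.9 | 70% |
| 90% / 95% | 9.5 | 59% |
| 85% / 95% | 7.3 | 39% |
| 80% / 95% | 5.0 | 21% |

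**Step 3: no true effect.** With success 0.55 in both arms, the expected difference is 0.45 × (s for TAU − s for SIRI).
- 90% / 95%: −2.25 points, and about a 7% chance of a significant result against SIRI (nominal 2.5%).
- 85% / 95%: −4.5 points, and about 17%.
- Equal detection: 2.5% on each side.

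**Step 4: what these rates require.** The success rule applies only to lost participants. Suppose a share L is lost in each arm, lost and retained participants have the same failure risk, and every failure among the retained is found. Then s = 1 − L × (1 − share found among the lost), so the share found among the lost = 1 − (1 − s)/L.
- 90% / 95% overall needs 67% / 83% among the lost if L = 30%, and 50% / 75% if L = 20%.
- 85% / 95% overall needs 50% / 83% if L = 30%, and 25% / 75% if L = 20%.
- 80% overall in TAU needs 33% if L = 30%, and 0% if L = 20%.

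The last two rows of the table therefore call for large gaps among the lost. The 90% / 95% row needs a smaller gap, but is still only an assumption.

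**The case against.** The strongest reply is that the common search is good. Everyone has index EHR and exchange queries, baseline releases, an outreach worker who checks records and the coroner, and a later look-back. The sentence on record monitoring explains why the intervention rarely stops early, and names no data source beyond those searched for everyone. This stands as a limit on size. It does not remove the mechanism: baseline releases cover only the systems usually visited, further records depend on self-report, coroner and medical examiner checks are local, and tracing and contact with other hospitals are extra in one arm.

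Some stronger readings are tempting, but the documents do not support them.
- A reader might infer that the primary comparison is shown to be biased. No detection rate is given and the shared search may find nearly everything, so the text supports an expectation and a direction only.
- A reader might infer that the success rule must be replaced by proof of being alive and observed at day 122, with all others missing. That carries its own bias, because a failure would need one record while a success would need later contact, which SIRI supplies more often. Suppose true success is 55% in both arms, all failures are found, and 80% (SIRI) and 60% (TAU) of successes are confirmed. Observed success is then 0.44/0.89 = 49.4% against 0.33/0.78 = 42.3%, a spurious 7 points for SIRI.
- A reader might infer that events before withdrawal are discarded. The article says without exception that a confirmed event is a failure, and lists withdrawals only as where missing data are anticipated. At most the order of precedence needs stating.
- A reader might infer that no sensitivity analysis is planned. The full protocol and SAP are not shown, so this cannot be counted.

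**Conclusion.** The point holds as a likely asymmetry of unknown size. The plan scores unknown as success, and the intervention adds surveillance in one arm during the endpoint window. SIRI failures can be expected to be found somewhat more completely, which works against the intervention. Through this mechanism a false benefit is not the worry; a diluted effect or apparent harm is.

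An assumed five-point gap in detection (90% against 95% of all failures) turns 12.4 points into about 9.5 and 80% power into about 59%. This rests on 240 per arm, the 0.55 row of Table 3, and SIRI team knowledge reaching the outcome data. With detection near complete in both arms, the loss is small.

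The Discussion's statement that the outcome is available regardless of loss to follow-up needs qualifying: where no record exists, it is available only because unknown is defined as success.

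**What to change.** 1. Ascertain the primary outcome in both arms by one identical, dated record search at a fixed time after day 122: index EHR, health information exchange, baseline-signed releases, medical examiner and contacts. Where feasible, have existing abstractors unaware of arm do it.
2. Add a sensitivity analysis that counts only events found by that search.
3. Add an arm-specific tipping-point analysis that varies the assumed failure rate among lost participants scored as successes.
4. Keep the rule that no record means success for the primary analysis, and qualify the availability statement in the Discussion.
5. State in one sentence that a death or readmission documented before withdrawal counts as a failure.

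Cost: wording and modest extra analysis. The searches are already planned and need a common date. Events known only through SIRI team contact are left out of the sensitivity analysis in item 2, so it should be read beside the primary result and not in its place.

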**Methods:**

The Holistic Intervention for Severe Injection-Related Infections (HI-SIRI) trial is a multicenter, randomized controlled trial conducted at six academic hospitals across the United States with two parallel treatment arms. Participants (*N* = 480) hospitalized with confirmed or suspected SIRI and injection drug use in the past year will be randomized to either the “SIRI team” intervention or treatment as usual (TAU) arm. Randomization will be stratified by site, primary drug (opioid vs. non-opioid), and ICU admission. The primary trial outcome is the difference in the proportion of participants alive with no hospital readmissions at 4 months post-randomization between the two arms. Secondary outcomes include SUD and ID treatment initiation, antibiotic treatment completion, all-cause and substance use related mortality, and overall healthcare utilization, assessed at 8 and 12 months post-randomization. A cost-effectiveness analysis and implementation evaluation will also be performed.

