Non-fatal overdose	Combination of medical record abstraction and self-report	4, 8, and 12 months
Mortality All cause •All cause •Substance use-related (SIRI, overdose)	Combination of medical record abstraction and other sources (e.g., coroner’s report)	Continuous
Substance use severity and frequency	Drug Abuse Screening Test, Alcohol Use Disorders Identification Test, and Addiction Severity Index	4, 8, and 12 months
Initiation of SUD treatment before hospital discharge •MOUD •MAUD	Medical record abstraction	n/a
Initiation of ID treatments before hospital discharge • ART/PrEP • HCV DAAs • Immunizations	Medical record abstraction	n/a
Receipt of post-discharge SUD treatments •MOUD •MAUD •Intensive outpatient •Mutual support •Residential treatment	Combination of medical record abstraction, self-report, and urine test for methadone and buprenorphine	4, 8, and 12 months
Receipt of post-discharge infectious disease treatments	Combination of medical record abstraction and self-report	4, 8, and 12 months
Service utilization measures •Length of stay •Patient directed discharge •Readmissions (count and binary) •ED visits (count and binary)	Combination of medical record abstraction and self-report	4, 8, and 12 months

ED, emergency department; HCV DAAs, hepatitis C virus direct acting antivirals; HIV, human immunodeficiency virus; MAUD, medication for alcohol use disorder; MOUD, medication for opioid use disorder; PrEP, HIV pre-exposure prophylaxis; SIRI, severe injection-related infection; SUD, substance use disorder

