### Statistical analysis

#### Sample size and power analysis for efficacy outcome

Effect size was estimated for fixed power and sample size using PASS 2020. Since the true proportion of success in each treatment group is unknown, effect size was calculated for 80% power, a sample size of 480, and varying proportions of success in the TAU treatment group from 0.35 to 0.70 in steps of 0.05. Effect size was estimated using a logistic regression model for a binomial outcome with a logit link. The stratification factors used at randomization (site, type of primary drug use and admission to ICU as part of the index hospitalization) were not included in the power calculation model and therefore the power estimates are conservative. However, the stratification factors will be included in the analysis model at the analysis stage as fixed effects to improve the precision of the estimates. Table 3 shows the estimated effect size for varying proportions of success in the TAU treatment arm. The resulting risk differences and odds ratios corresponding to the proportions of success are also included for interpretation of the varying effect sizes. For a sample size of *N* = 480, there is 80% power or more for an absolute risk difference of 12.8% regardless of the level of success in TAU.

**Table 3 Tab3:** Power calculations for primary outcome based on potential rates of success in treatment as usual group

Sample Size	Power	Proportion of Success in		Risk	Odds
		TAU	SIRI team	Difference	Ratio
480	0.80	0.350	0.476	0.126	1.684
		0.400	0.527	0.127	1.672
		0.450	0.578	0.128	1.669
		0.500	0.627	0.127	1.678
		0.550	0.674	0.124	1.695
		0.600	0.721	0.121	1.721
		0.650	0.766	0.116	1.764
		0.700	0.810	0.110	1.825

SIRI, severe injection-related infection; TAU, treatment as usual

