#### Analyses of primary and secondary outcomes

A logistic regression model will be employed: alive and no hospital readmission (excluding elective treatment/procedures, detoxification-only or psychiatric admissions to a specialty hospital) OR any hospital readmission or death since previous visit as implemented in SAS. The test of the primary hypothesis will be achieved using the Wald test associated with the coefficient on the treatment indicator with the outcome at the 4-month follow-up. The model will include fixed effects for treatment group, site, type of primary drug use (opioid versus non-opioid), and admission to ICU as part of the index hospitalization (ICU versus non-ICU). The primary outcome hypothesis that the proportion of participants alive with no hospital readmissions will be higher in the SIRI Team intervention group vs. TAU group at four months post-randomization will be evaluated using a two-sided test with an a priori alpha (i.e., type I error) of 0.05. Since odds ratios can exaggerate interpretation of relative risk, particularly with larger incidence of the outcome, a Poisson distribution with log link and robust standard errors may also be considered to estimate the risk ratio directly.

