Additional secondary analyses will utilize the methods for the primary analysis if they are a single dichotomous outcome. If they include repeated measures, they will follow the analysis strategy of the above secondary outcome description.

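### The rule for single binary secondary outcomes makes no exception for sparse events, and its Wald test gives no usable result when an arm has none

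*Protocol article*

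**What the plan says.** The section *Analyses of primary and secondary outcomes* gives a default for the remaining secondary outcomes: "Additional secondary analyses will utilize the methods for the primary analysis if they are a single dichotomous outcome". Outcomes with repeated measures go instead to the logit GEE model described just before. No exception is made for few events or for an arm without events.

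The same section defines the primary method. It is a logistic regression in SAS: "The model will include fixed effects for treatment group, site, type of primary drug use (opioid versus non-opioid), and admission to ICU". On the test it says: "The test of the primary hypothesis will be achieved using the Wald test associated with the coefficient on the treatment indicator". The primary hypothesis is "evaluated using a two-sided test with an a priori alpha (i.e., type I error) of 0.05". A Poisson model with log link and robust standard errors is mentioned as an option, but its purpose is to give a risk ratio, not to handle sparse data.

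Table 2 lists the secondary outcomes. Several have a single assessment before discharge: starting medication for opioid or alcohol use disorder, ART or PrEP, hepatitis C antivirals, and immunizations. Mortality is listed as all-cause and as an item beginning "Substance use-related (SIRI, overdose", with the time point given as *Continuous*. The article states no expected rate for any of these outcomes.

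**The concern.** The method was planned around a common outcome. The power section says that "effect size was calculated for 80% power, a sample size of 480, and varying proportions of success in the TAU treatment group", and those proportions run from 0.35 to 0.70. The default then carries this model over to outcomes that may be of a different kind.

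The article itself suggests that some may be sparse. Under *SIRI team inpatient care*, the hospital work on chronic hepatitis C is to obtain baseline tests so that treatment can follow in the outpatient setting. Few or no inpatient starts in an arm is therefore plausible. Inpatient ART is offered only to participants living with HIV. Substance use-related death is a subset of all deaths.

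If an arm has no events, maximum-likelihood logistic regression has no finite treatment estimate. The Wald p-value then goes to about 1 however many events the other arm has, and there is no usable odds ratio or interval. With few events in both arms, the Wald test is conservative and loses power. A replacement method would then have to be chosen after the data are seen, in a trial that is not blinded.

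**Working it through.** **Inputs.** From the article: N = 480, two-sided alpha 0.05, and a trial "conducted at six academic hospitals across the United States with two parallel treatment arms". Assumed: 1:1 allocation (240 per arm), the event risks, and the covariate mix in the simulations.

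**Parameter count.** Intercept 1 + treatment 1 + site 5 + primary drug 1 + ICU 1 = 9.

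**The plan's own figure reproduces.** For Table 3, row 0.450 v 0.578, with 240 per arm:
- Pooled SE = √(2 × 0.514 × 0.486 / 240) = 0.0456.
- Unpooled SE = √((0.45 × 0.55 + 0.578 × 0.422) / 240) = 0.0453.
- Power = Φ((0.128 − 1.96 × 0.0456) / 0.0453) = Φ(0.85) = 0.80.

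All eight rows give 0.798 to 0.803. Even in the last row (0.70 v 0.81), the rarer result, failure, is expected 240 × 0.30 + 240 × 0.19 = 118 times. Nine parameters are no problem there.

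**An arm with no events.** Take 0 v 8 events in 240 per arm.
- Fisher: p = 2 × (240/480)(239/479)…(233/473) = 2 × 0.00368 = 0.0074.
- Unadjusted score: z = (8/240) / √((8/480)(472/480)(2/240)) = 0.0333 / 0.0117 = 2.85, p = 0.004.
- Nine-parameter logistic fit: coefficient about −23, SE about 21,200, Wald p = 0.999.
- Firth with the same covariates: finite odds ratio, p about 0.002 to 0.003 depending on the simulated covariates.

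**How often an arm is empty.** P(no events in 240) = (1 − p)^240, which is 30% at p = 0.5%, 9% at 1% and 0.8% at 2%.

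**Power of the nine-parameter model.** These are separate simulations with different assumed covariate mixes. An empty arm counts as no Wald rejection, and ranges are across runs.

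| Assumed risk, TAU v SIRI | Expected events | Wald | Firth |
|---|---|---|---|
| 2% v 0.5% | 6 | 4.5–6% | 25–29% |
| 3% v 0.5% | 8.4 | 19–24% | 53–58% |
| 3% v 1% | 9.6 | 19–21% | 31–34% |
| 4% v 1% | 12 | 43% | 56% |
| 5% v 2% | 16.8 | 40–43% | 43–46% |

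Expected events are 240 × (sum of the two risks). In one of these simulations, type I error at 2% risk in both arms was 1.9% for Wald and 4.1% for Firth. At 1% it was 0.1% and 2.1%.

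**Where the loss ends.** Exact unadjusted power, Wald against score: 6% v 2% (19.2 events) 0.58 v 0.63; 8% v 2% (24 events) 0.86 v 0.88; 12% v 5% (40.8 events) 0.79 v 0.80.

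**The case against.** The strongest objection is that this is detail for the full protocol or the analysis plan. The article condenses Protocol 4.0, which is not shown, and a fallback for sparse data is often specified elsewhere. That would answer a complaint that something is missing. Here, however, the article states a rule for every single binary secondary outcome and names the test. Applied as written, the rule gives a wrong answer in a foreseeable case. An analysis plan may already contain the exception; if so, the article's sentence should not read as universal.

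The second objection is that rarity is assumed. This stands. The largest losses come from risks of 3% or less with large relative reductions, and the article gives no rates. Its *Background* describes these admissions as being at the severe end of the risk range, so all-cause death over 12 months may well exceed 20 events.

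Third, a reader might infer that the plan will miss a real difference in drug-related death, or that it throws away the dates of death. The documents support neither. Table 2 gives mortality the time point *Continuous*, which fits neither branch of the default clearly, and nothing says that deaths are reduced to one binary endpoint. What can be said is narrower: the routing of mortality is unclear, and the logit GEE branch would also have no finite estimate with an empty arm. Nor does a time-to-event model follow as the remedy, since cause-specific death would need deaths from other causes handled as competing events.

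Fourth, a standard error near 20,000 would be noticed. That is true, but the rescue method would then be chosen after seeing the data.

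Finally, Firth is not uniquely best. In one of the nine-parameter simulations the score test had slightly more power (0.59 v 0.53 at 3% v 0.5%) and held its size better. The fix should allow for this.

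**Conclusion.** The point holds for sparse binary secondary outcomes only. With an empty arm, the stated Wald test is unusable whatever the other arm shows. Below about 10 to 12 events in total it loses much of its power, roughly 21% against 57% for Firth at 3% v 0.5% and 20% against 33% at 3% v 1%. By about 17 events (5% v 2%) the gap is around 3 points, and from about 20 it is negligible. These sizes rest on assumed risks, 240 per arm and simulated covariates; the failure with an empty arm needs none of those risk assumptions. It applies most directly to the pre-discharge treatment starts, and to substance use-related death only if that is analysed as a single binary outcome. The primary outcome is unaffected. This is a worthwhile low-cost correction, not a threat to the main result.

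**What to change.** Keep the primary method as the default for common binary secondary outcomes, and add one sentence to that rule. A binary secondary outcome with no events in an arm, or with fewer than a pre-set total (for example 20), is analysed by Firth penalised logistic regression with the same covariates, using the profile penalised-likelihood test and interval. A score or exact test is an acceptable alternative if named in advance. An exact test cures the empty-arm failure but recovers less power: unadjusted Fisher has 0.42 at 3% v 0.5% and 0.23 at 3% v 1%. State also which branch of the default mortality follows.

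The cost is a sentence and an option in the SAS procedure for logistic regression, with no new data. The downside is a slightly shrunken estimate. The threshold of 20 is a judgement, placed where the two tests come close to agreeing.
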